#### Control

This group will receive a written participant information and consent form based on a hypothetical trial, using the template for interventional studies mandated by the Victorian State Government. The content of the consent form has been informed by Australia’s National Statement on Ethical Conduct in Human Research (NHMRC 2007) (see Additional File 2).

#### Intervention

In addition to the written participant information and consent form, participants randomised to the intervention arm will be provided with a 6-min-long video animation that explains a hypothetical trial in plain English. Content for the hypothetical trial is based on previously published placebo-controlled trials of ASD and informed by qualitative interviews with orthopaedic patients about their understanding of and attitude towards placebo-controlled surgical trials. The video animation will invite participants to take part in a hypothetical placebo-controlled trial of ASD. It will describe the procedure, the need for further research, what a placebo-controlled surgical trial involves, and trial participation requirements. It will also describe key concepts such as equipoise, placebo effects, randomisation, and blinding. All information represented in the consent video will also be contained in the written form.

### Outcomes

#### Primary outcome

The primary outcome is the proportion of participants who state that they would be willing to opt into the hypothetical ASD trial after being presented with the relevant consent materials. As is common with complex trials, participants will be encouraged to review and discuss trial information before, during, and after consenting to participate. Therefore, outcome measures will be collected immediately after participating in the informed consent process (*t*_2_) and at a second time-point 1 week after completion of the consent process (*t*_3_).

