Amongst the most commonly reported reasons for poor recruitment to surgical RCTs include difficulty understanding and a negative attitude towards trial concepts, and a preference for one form of treatment [14]. In line with these findings, Isaksson et al. [15] identified the two most important factors for enhancing recruitment in a RCT as (1) the research question needs to be considered important and (2) a simple procedure for providing information and gaining consent. One such strategy identified to help improve informed consent and therefore enhance recruitment includes the use of video animation. There is some evidence of the positive impact of video animation on enhancing patients’ understandability of research and attitude about participation in clinical research [16–19]. While two studies have shown that the use of educational videos do not, on their own, have a substantial impact on patients’ willingness to enrol in cancer-related trials [16, 17], the use of animated consent materials for placebo-controlled surgical trials has not been explored.

The challenges faced by previous trials highlight the pressing need to carefully evaluate the feasibility of placebo-controlled surgical trials early in the trial planning process. During the process of establishing the feasibility of such trials, there is also an imperative to assess the impact of concrete interventions that aim to optimise the trial’s likelihood of success. Moreover, there is a need to explore new avenues to optimise the feasibility of planned trials by engaging with key stakeholders. Taken together, these considerations provide a framework for this mixed-methods feasibility study, which aims to address the following questions.
*Feasibility*. What proportion of patients who have consented to undergo ASD report that they would be willing to enrol in a placebo-controlled trial for this procedure?*Optimisation*. Can patients’ willingness to enrol in, or understanding of, such a trial be improved by supplementing written consent materials with a brief visual animation that outlines the details of the trial?*Exploration*. What factors influence patients stated willingness to enrol in such a trial, and how do they believe the recruitment process could be improved?

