### Participants

Given orthopaedic surgeons in Australia often work in both public and private settings, participants will be identified from the SVHM orthopaedic public clinic lists and from the private rooms of surgeons who conduct surgery at SVHM. Individuals will be consented to participate in the feasibility study via telephone call with a member of the research team. After approximately 1 week, individuals will be contacted again to confirm participation. Patient-specific health and sociodemographic information will be collected to test for relevant differences between patients in each arm of the trial. A set of three questions will be used to assess functional health literacy (adapted from Ghanouni et al. [22]). These questions will specifically measure participants stated ease of understanding of medical statistics and written information, and an objective numeracy measure. In addition, we will measure trial literacy using the Therapeutic Misconception Scale. A measure of the participants’ general health status, including both physical and mental health, will be derived using the VR12 [23]. Symptom severity will be derived from a validated questionnaire (Oxford Shoulder Score [24]).

A subset of purposively sampled participants that represent a range of ages and gender from each study arm (approximately 20 in total) will be invited to participate in a phone audio-recorded qualitative interview. After the collection of all other outcome data, these participants will be asked to review the consent material (either written or video animation) while verbalising their immediate responses to these materials, using a ‘think aloud’ technique [25]. This will provide insight into how participants understand key concepts about the study design such as randomisation, blinding, and the use of placebo controls [26].

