### Randomisation and masking

To minimise bias, participants will be informed that the study aim is to explore patient understanding of informed consent procedures for a placebo surgery trial, but specific details about differences between these consent procedures will not be provided. Participants will only receive information on the mock trial arm they are randomised to and will receive no information about the comparator arm for the duration of the study. After being consented to this feasibility trial, participants will be randomly assigned in a ratio of 1:1 to either arm of the trial. Block randomisation will be performed by an investigator not involved in participant recruitment using computer-generated random assignment sequence prepared in blocks of four and stored in a password-protected file. A research assistant independent of recruitment and data collection will be responsible for participant management. The research associate (who will be responsible for patient consent) will be blinded to group allocation at the time of consent. In addition, outcome ascertainment will be blinded. Upon completion of the study, a biostatistician blinded to group allocation will analyse outcome data.

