## Discussion

The proposed study will provide evidence that will inform the planning and design of future placebo-controlled surgical trials. Not only will it provide information about the proportion of patients that can be expected to enrol in such a trial, which is directly relevant to its overall feasibility, it will also provide insights into whether recruitment could be optimised through the use of supplemental animated consent materials. By embedding a qualitative investigation into this study, we hope to gain further insights into other barriers and anxieties faced by patients when considering participation in such a trial. This will provide important information for educating researchers involved in the recruitment process. Even in trials that are otherwise feasible, improving the patient recruitment process is likely to reduce both the time and funding needed to conduct the trial. Although these findings will be relevant to many forms of placebo-controlled surgical trials, they are likely to be most generalisable to trials of ASD.

More generally, this study will contribute to our understanding of whether the use of animated consent materials improves trial recruitment. While two studies have shown that the use of educational videos do not, on their own, have a substantial impact on patients’ willingness to enrol in cancer-related trials (Du et al. 2008, 2009), the use of animated consent materials for placebo-controlled surgical trials has not been explored. Moreover, the only available study to assess the impact of providing a brief video in addition to written information showed that such supplemental information significantly increased willingness to enrol in a trial involving pregnant women with pre-labour rupture of membranes (Weston, Hannah, and Downes 1997). Importantly, this trial does not simply hope to test whether such supplemental information is likely to improve recruitment, it will also assess the impact of such interventions on patients understanding of the trial to which they are consenting. Improved understanding of such trials allows patients to more appropriately express their autonomy, which is vital to the ethical conduct of clinical research.

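### The feasibility question is about patients consented for ASD, but the primary outcome counts only those who first agreed to join this study, and no proportion of patients approached is defined

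*Protocol article*

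**What the plan says.** The first research question, at the end of the Background, asks: "What proportion of patients who have consented to undergo ASD report that they would be willing to enrol in a placebo-controlled trial". The population is everyone consented for the operation.

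The Primary outcome section uses a different base: "The primary outcome is the proportion of participants who state that they would be willing to opt into the hypothetical ASD trial". Entry is described under Participants: "Individuals will be consented to participate in the feasibility study via telephone call with a member of the research team". Under Randomisation and masking, "participants will be informed that the study aim is to explore patient understanding of informed consent procedures for a placebo surgery trial". The Timelines section places an emailed information form and a telephone explanation before verbal consent. Allocation comes later: "After being consented to this feasibility trial, participants will be randomly assigned in a ratio of 1:1 to either arm of the trial". Table 1 lists the measure as a recruitment rate, at two time-points that both follow allocation.

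The Discussion says that the study will "provide information about the proportion of patients that can be expected to enrol in such a trial". Its limitations paragraph accepts that willingness may be over-estimated and treats the rates as a probable upper limit. The only reason it gives is that participants are considering a hypothetical trial.

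**The concern.** The question, the outcome and the interpretation do not share a denominator. The question and the interpretation refer to patients; the outcome refers to patients who have already accepted an invitation to research on placebo surgery. Someone who dislikes research, or the idea of placebo surgery, can leave at the telephone call and is never asked the outcome question. The step that filters people into the denominator may therefore be related to the quantity being measured.

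This matters because of what the number is for. The Background motivates the study with two placebo-controlled ASD trials whose recruitment ran far beyond plan and needed many more sites. The feasibility proportion is the output that a future trial team would use to plan sites and recruitment time. An upper limit with no lower figure beside it gives them little to plan with.

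**Working it through.** **No figure to reproduce.** The article states a target of 40 per arm (2 × 40 = 80) and no power or precision calculation. It gives no expected proportion willing and no expected uptake.

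**Inputs.**
- n = 80 participants, from the Sample size justification, all assumed to give the outcome.
- w, the proportion willing among participants: assumed to be 48/80 = 0.60.
- N, the eligible patients approached: assumed to be 100, 120 or 160. Uptake f = 80/N is then 0.80, 0.67 or 0.50.
- w0, the proportion willing among those who decline this study: unknown. It is set to 0, to half of w (0.30), and to w (0.60).

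**Formula.** Willingness among all patients approached is f·w + (1 − f)·w0. The excess of the reported proportion over this is w − [f·w + (1 − f)·w0] = (1 − f)(w − w0). It is zero if everyone approached joins (f = 1) or if decliners are as willing as participants (w0 = w). It is positive only if w0 < w.

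**Results.**

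| Approached | Uptake f | All approached, w0 = 0 | All approached, w0 = 0.30 | All approached, w0 = 0.60 | Overstatement in points (w0 = 0 / 0.30 / 0.60) |
|---|---|---|---|---|---|
| 100 | 0.80 | 48/100 = 48% | 48% + 0.20 × 30% = 54% | 60% | 12 / 6 / 0 |
| 120 | 0.67 | 48/120 = 40% | 40% + 0.33 × 30% = 50% | 60% | 20 / 10 / 0 |
| 160 | 0.50 | 48/160 = 30% | 30% + 0.50 × 30% = 45% | 60% | 30 / 15 / 0 |

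The w0 = 0 column is a floor: willingness among those approached cannot be lower than this, whatever the decliners would have said.

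**Against sampling error.** The Wilson 95% interval for 48/80 is 49% to 70%. All three floor values lie below it. With decliners half as willing, 54% and 50% lie inside it and 45% lies outside. A confidence interval around the participant proportion therefore need not cover the proportion among patients approached, but whether it misses depends on f and w0.

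**The contact at about one week.** The Participants section also mentions a call after about a week to confirm participation. Its timing matches the second outcome assessment, which follows the first, so it is not clearly a further filter before the outcome. It is not counted here.

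**The case against.** The strongest reply is that the reader is already warned. The limitations paragraph calls the rates a probable upper limit, and self-selection would most likely push the same way, so that reading survives. What is missing would then be one more reason for an acknowledged bias. This has force and limits the seriousness of the point. It does not dispose of it: selection by prior consent would remain even if stated willingness predicted behaviour perfectly, the denominator still differs from the one in the question, and no lower figure is offered.

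Second, people may decline for unrelated reasons, such as the two half-hour sessions, and they are not being asked to undergo placebo surgery. That is correct. A reader might infer that the outcome is certain to overstate willingness; the document has no data on decliners, so the direction is an inference.

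Third, a condensed article commonly leaves screening logs and flow counts to the full protocol, and this one commits to SPIRIT and the CONSORT extension for pilot trials. Nothing suggests that decliners will go uncounted, and the absence of a log is not the point. Flow counts alone, however, change neither the defined outcome nor the Discussion's reading of it.

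Fourth, nobody can record the willingness of people who refuse to be asked. Counting them as unwilling is a convention, which is why the result must be labelled a lower bound.

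A reader might also infer that one proportion will be averaged over both arms, mixing two consent processes. No section specifies this: the design is two-arm and the analysis section gives tests for comparing groups.

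**Conclusion.** The mismatch stands on the text. The research question and the Discussion concern patients consented for ASD; the primary outcome concerns those who agreed to join this study. The stated upper-limit caveat rests on a different reason and does not repair the denominator.

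That the proportion is too high is plausible but conditional on decliners being less willing than participants. The size is unknown because uptake is not given. In the illustration the overstatement runs from zero up to 12, 20 or 30 points at assumed uptakes of 80%, 67% and 50%. It would be wrong to read 12 to 30 points as the estimated bias: those are the maxima, reached only if no decliner would be willing. With decliners half as willing the figures are 6, 10 and 15.

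The comparison of video plus written material with written material alone keeps its internal validity, because this selection happens before randomisation. The point touches only the absolute proportion. It is worth correcting because that proportion answers the study's first question and the correction is cheap.

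**What to change.** 1. Count eligible patients approached, declining and enrolled. Counts are enough; no further data on people who decline are needed.
2. Report stated opt-in among participants, as now defined, and also among all eligible patients approached, with those who decline this study counted as not willing. Label the second figure a lower bound for stated willingness. Decliners leave before allocation and belong to neither arm, so the bound is the participant proportion multiplied by uptake.
3. In the limitations paragraph, name selection by prior consent to research as a second reason why the participant proportion may be too high.
4. In the Discussion, present the range between the two figures in place of a single proportion of patients expected to enrol. Keep the existing caveat that stated willingness in a hypothetical trial may exceed actual enrolment: the lower bound concerns stated willingness and is no floor for real recruitment.

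The cost is a tally kept by the staff making the calls and one extra table. No additional participants or visits are needed. The downside is a lower figure that looks less favourable.

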#### Secondary outcome

The secondary outcome, trial literacy, will be assessed using the Therapeutic Misconception Scale [27]. Therapeutic misconception occurs when research participants fail to distinguish between the imperatives of clinical research and ordinary treatment. Therapeutic misconception is detrimental to a participant’s understanding of a study, which is crucial for autonomous decision-making [27].

### Sample size justification

As a feasibility study, no formal power calculation is needed [28]. Based on recommendations for sample sizes for feasibility studies [29], we have set a maximum target of 40 participants per arm (approximately 80 in total) to ensure adequate representation of males and females from both public and private hospital settings. In qualitative research, data collection and data analysis are conducted in parallel and the sample size is determined by thematic saturation. As such, an a priori sample size calculation is not appropriate as it is not possible to know in advance when saturation will be reached. Previous qualitative studies embedded in orthopaedic trials have reached saturation at 12 [30] to 18 participants [31]. Therefore, the sample size of 80 participants will also be sufficient to enable the embedded qualitative evaluation.

### Randomisation and masking

To minimise bias, participants will be informed that the study aim is to explore patient understanding of informed consent procedures for a placebo surgery trial, but specific details about differences between these consent procedures will not be provided. Participants will only receive information on the mock trial arm they are randomised to and will receive no information about the comparator arm for the duration of the study. After being consented to this feasibility trial, participants will be randomly assigned in a ratio of 1:1 to either arm of the trial. Block randomisation will be performed by an investigator not involved in participant recruitment using computer-generated random assignment sequence prepared in blocks of four and stored in a password-protected file. A research assistant independent of recruitment and data collection will be responsible for participant management. The research associate (who will be responsible for patient consent) will be blinded to group allocation at the time of consent. In addition, outcome ascertainment will be blinded. Upon completion of the study, a biostatistician blinded to group allocation will analyse outcome data.

### Timelines

The anticipated start date of November 2020 and end date of December 2021. A summary for SPIRIT schedule of study including enrolment, intervention, and assessment is shown in Table 1.
Patients will receive a participant information form (via email) and given a verbal explanation of the project via telephone. Patients will be consented to be a part of this trial using a verbal consent script, which will be audio-recorded and documented (see Additional file 2).At this point, patient-specific health and sociodemographic information will be collected.Once participants have agreed to be a part of the study, they will be randomly assigned to view one set of the consent materials for the hypothetical placebo-controlled ASD surgery trial.The main outcome measure will be participants stated willingness to opt-in to the hypothetical placebo-controlled shoulder surgery trial.Participants will also be asked a series of questions about their understanding of the information presented.This information will be collected at two time-points: immediately after reviewing and discussing the trial information with a researcher, and again approximately 1 week after completion of the consent process: 2 × 30-min sessions.After the collection of outcome measures, a purposively sampled subset of participants will participate in qualitative interviews.

**Table 1 Tab1:** SPIRIT Trial study schedule of enrolment, interventions, and assessments

Time-point	Enrolment	Randomisation	Post-allocation			
	***− t***_**1**_	0	***t***_**1**_	***t***_**2**_	***t***_**3**_	***t***_***4***_
**Enrolment**						
**Baseline data, demographics**	X					
**Eligibility screen**	X					
**Informed consent**	X					
**Allocation**		X				
**Participant characteristics**						
**Health literacy**	X					
**General Health**^**a**^	X					
**Symptom Severity**^**b**^	X					
**Interventions**						
**Video animation**			X			
**Written information**			X			
**Assessments**						
**Recruitment rate**				X	X	
**Therapeutic misconception**^**c**^				X	X	
**Qualitative study**						
**Think aloud interview**						X

^a^VR-12

^b^Oxford Shoulder Score

^c^Therapeutic Misconception Scale

### Data management

All data will be stored on a password-protected computer kept in a secure locked facility and only accessible to the research investigators and the trial coordinator as approved by the SVHM Human Research Ethics Committee (HREC). At the completion of the study, outcome data will be pooled and de-identified for analysis by a statistician. Due to the short duration and minimal risks of the trial, there will not be a data monitoring committee. However, the principal investigator will be responsible for overseeing the trial and ensuring data quality and completeness, including participant enrolment, consent eligibility and forms, allocation to study groups, data recording and timeliness of data collection. Furthermore, there will be no planned interim analyses and stopping guidelines.

### Analysis

#### Quantitative analysis

Categorical variables will be analysed using chi-square tests. For continuous variables, we will employ (parametric) *t* tests and (non-parametric) Mann-Whitney tests for symmetrically and asymmetrically distributed data, respectively. Analyses will be conducted on an intention-to-treat basis by a blinded statistician using Stata, version 14.0 (StataCorp, College Station, Texas).

